#### Exclusion criteria

The exclusion criteria are as follows:

Patients with connective tissue disorders or myositis conditionHistory of any Hip & Knee surgeryPatients with malnutrition were assessed by Mini-Nutritional assessment.Patients with acute immobility (i.e., post-hip fracture or post-acute hospital admission)Patient scheduled for TKR within six monthsPatients already taking vitamin D supplementsPatients with a known contraindication to vitamin D treatment (such as allergy)Patients who have renal impairment with glomerular filtration rate < 30 ml/minute

### Recruitment

Based on the inclusion and exclusion criteria, qualified patients will be recruited from the outpatient clinic with written permission from the Prince of Wales Hospital’s Department of Orthopaedics and Traumatology. Additionally, the center’s employees will help find qualified patients and refer them to us for screening. Then, they will then be randomly using a computer randomization program to allocate the participants as either to receive the vitamin D supplement or placebo The following basic patient demographics will be noted: age, gender, ethnicity, occupation, BMI, and alcohol and tobacco use. The Clinical Management System, Hospital Authority, the main computerized database for Hong Kong’s public hospitals, will also be used to verify and record medical histories.

### Informed consent

Before participants takes part in the study, trained research assistants will get their written and oral informed permission. First, eligible participants will receive a thorough explanation of our study from our research assistants. All patients must give their informed consent in order to attend the trial. The Declaration of Helsinki will be followed in the conduct of the study. The ethics committee has granted ethical approval.

Informed consent also covers agreement for biological specimens and participant data. Each participant will be assigned an ID number, and private information like name, address, and phone number will be kept private before, during, and after the research.

### Randomization and allocation concealment

A total of 56 patients will be enrolled. Participants will be randomized into 1:1 allocation, blocked randomization with 28 participants in the Vitamin D group and 28 participants in the control group. An independent research staff will assign participants to interventions.

The randomization will be done using a computer randomization program by an independent statistician before the intervention. To ensure blindness, a randomization code will be assigned to every participant. Only once the database has been locked will the randomization code be broken. Assessment and data analysis are conducted by different research staffs blinded to the patient’s randomization assignment.

### Blinding

The participants’ group assignment will remain a secret to all parties involved—the researchers, statisticians, research assistants, and patients—during the study and assessment. The research assistant who assists in obtaining consent oversees the study’s advancement and reports any adverse events will not be involved in the data analysis. The assessor, a distinct knowledgeable research assistant, will not be blind to the randomization status and will not participate in the intervention. The statistician responsible for the randomization process is not involved in the data analysis or other project-related tasks.

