## Abstract

Osteoarthritis (OA) knee is one of the most common chronic degenerative conditions that imposes clinical and economic burdens on individuals and societies worldwide. Previous studies showed vitamin D levels correlated positively with lean muscle mass and grip strength, implying that vitamin D supplementation may improve muscle health in knee OA subjects. This randomized controlled trial (RCT) aims to compare the effects of vitamin D supplementation on knee muscle strength, physical function, pain, and sarcopenia status in patients with end-stage knee OA. Patients and outcome assessors will be blinded to group allocation. Fifty-six end-stage knee OA patients with vitamin D insufficiency fulfilling our inclusion criteria will be invited to participate in this study. Patients will be randomly assigned to take vitamin D supplementation (4,000 IU capsule daily) or placebo for six months. Measurements will be taken at baseline, three and six-month after the commencement of the vitamin D supplement, and 6-month after the interventional period. The primary outcome includes the isometric quadriceps and hamstring muscle strength measured by a hand-held dynamometer. Secondary outcomes include pain, performance-based and self-reported physical function and sarcopenia status. The success of this study will provide scientific evidence of whether the relatively cheap and well-tolerated vitamin D supplement can improve quadriceps muscle strength, physical function, pain symptoms, and sarcopenia status of this increasingly large population for end-stage knee OA patients. The study has great clinical significance given Hong Kong’s lengthy and growing waiting list for complete knee replacement procedures.

**Trial registration:** The trial was registered on clinicaltrials.gov (NCT05981534) on 31^st^ July 2023.

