### Trial design

The study is a randomized, double-blinded, controlled study that aims to compare the effects of vitamin D supplementation on knee muscle strength, physical function, pain, and sarcopenia status in patients with end-stage knee OA at 3 months and 6 months after the commencement of vitamin D supplement, and 6-month after the interventional period.

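### The Blinding section says the outcome assessor will not be blind, against the rest of the protocol, and the primary outcome depends on effort

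*Protocol article*

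**What the plan says.** The statements on blinding in the protocol article do not agree.

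- **Blinding, sentence on the assessor:** the assessor, described as a separate research assistant, "will not be blind to the randomization status and will not participate in the intervention".
- **Blinding, opening sentence:** the "group assignment will remain a secret to all parties involved". Research assistants are named among those parties, and the period covered includes assessment.
- **Abstract:** "Patients and outcome assessors will be blinded to group allocation".
- **Randomization and allocation concealment:** "Assessment and data analysis are conducted by different research staffs blinded to the patient"'s assignment. The same section adds: "Only once the database has been locked will the randomization code be broken".
- **Trial design:** "The study is a randomized, double-blinded, controlled study".

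Under Knee muscle strength, the primary outcome is maximal voluntary isometric quadriceps and hamstring strength, read from a hand-held dynamometer. The participant is told to push with full effort for five seconds, two trials are done, and the maximum force is noted.

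**The concern.** The sentence on the assessor is complete and operative, and it sits in the section that governs blinding. It states the reverse of what the Abstract and the randomization section promise, and of what the same paragraph says a few lines earlier.

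The nature of the outcome makes this serious. A maximal voluntary contraction depends on how the test is explained, how strongly the participant is urged on and how the device is placed. An assessor who knows the arm can differ on all of these without intending to. The chair stand, 6-meter gait speed and handgrip tests carry the same risk, and the last two also enter the sarcopenia definition. Identical capsules keep the participant blind but do not close this route, because the difference arises on the assessor's side.

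Detection bias of this kind is confounded with the treatment effect, so neither the ANCOVA nor the repeated-measures ANOVA can separate the two. A trial run in this way would also not be assessor-blinded as the Abstract claims, and its double-blind label would be open to challenge. The Trial status section says that recruitment began on 17 March 2024 and is continuing, so assessments may already have been made.

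**Working it through.** **Step 1. Set the statements side by side.**

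| Place in the protocol article | Is the assessor blind? |
|---|---|
| Abstract | Yes, stated outright |
| Trial design | Implied by the double-blind label |
| Randomization and allocation concealment | Yes: assessment staff are blinded, code broken only after database lock |
| Blinding, opening sentence | Yes: secret from research assistants during assessment |
| Blinding, sentence on the assessor | **No** |

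The assessor is described as a research assistant, so the first and later sentences of the Blinding section cannot both be true. If the assessor knew the allocation during the study, the rule that the code stays unbroken until database lock could not hold either. The section on unblinding does not resolve the conflict: it covers only release of the code after a major adverse event.

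**Step 2. Illustrate what an unblinded assessor could do.** The documents give no figure for assessor bias, so this step rests on assumptions and shows a range.

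Inputs:
- *n* = 28 per arm (Sample size calculation), with 23 per arm, the number before the attrition allowance, as the alternative.
- ANCOVA on the baseline value, two-sided 0.05 (Statistical analysis).
- Assumed: true effect zero.
- Assumed: baseline to follow-up correlation *r* = 0.5, with range 0.3 to 0.7.
- Assumed: differential assessor effect *b* of 0.2, 0.3 or 0.4 SD in favour of vitamin D.

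Formula: the chance of a significant apparent benefit is P(*T* > *t*crit), where *T* is noncentral *t* with df = 2*n* − 3 and noncentrality δ = *b* / √(1 − *r*²) × √(*n*/2).

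For *n* = 28 and *r* = 0.5: df = 53, *t*crit = 2.006, √(1 − 0.25) = 0.866 and √14 = 3.742, so δ = 4.320 × *b*.

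| *b* (SD) | δ | Chance, *n* = 28, *r* = 0.5 | Range over *r* = 0.3 to 0.7, *n* = 28 | *n* = 23, *r* = 0.5 |
|---|---|---|---|---|
| 0.2 | 0.864 | 0.133 | 0.12 to 0.18 | 0.12 |
| 0.3 | 1.296 | 0.246 | 0.21 to 0.34 | 0.21 |
| 0.4 | 1.728 | 0.396 | 0.34 to 0.54 | 0.33 |

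The nominal chance in that direction is 0.025.

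**Step 3. Allow for the Bonferroni correction.** The plan attaches Bonferroni to the ANCOVA but does not define the family. If it covers the three follow-up times, the two-sided level is 0.05/3 = 0.0167, or 0.0083 in one direction at each time. With *r* = 0.5, the chances for *b* = 0.2, 0.3 and 0.4 become 0.06, 0.13 and 0.24 with 28 per arm, and 0.05, 0.10 and 0.19 with 23 per arm. All are well above 0.0083.

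**The case against.** The strongest reply is that this is a one-word slip and not a chosen design. Every other statement on blinding points to a blinded assessor, the capsules are identical, allocation is in independent hands, and no passage describes how an assessor would learn the arm. On this view the finding is an internal inconsistency, and any bias is conditional on the sentence describing real conduct. That reading is probably right, and the condition stands. It does not remove the need for correction: the article leaves the matter open, and the stray sentence is the one that specifically sets out what the assessor does.

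The size is also open to challenge. The assessor effect and the correlation are assumed, its direction is taken to favour vitamin D, and the 13%, 25% and 40% figures fall with 23 per arm or a Bonferroni level. This stands, and the figures should be read only as an illustration. The contradiction does not depend on them.

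Some routes for bias are less firmly grounded than others. The protocol does not say who holds or steadies the dynamometer, and with two fixed trials and the maximum recorded there is limited room to choose among trials for the primary outcome. Instruction, encouragement and device placement remain. Finally, detail on custody of the code and on handling of 25(OH)D results may properly sit in the full protocol, so its absence from the article is not held against the plan.

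**Conclusion.** The concern holds. As written, the Blinding section unblinds the assessor of the primary outcome and contradicts its own opening sentence, the Abstract, the Trial design section and the section on randomization and allocation concealment. Nothing in the article resolves the conflict. It must be fixed because the trial is recruiting and bias introduced at measurement cannot be undone later.

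Whether harm has occurred is unknown and depends on actual practice. If the assessor has been blind throughout, the problem ends with the text. If not, assumed differential effects of 0.2 to 0.4 SD would raise the chance of a false benefit at a given time point from 2.5% to about 13% to 40% (28 per arm, *r* = 0.5, unadjusted level). With Bonferroni over three times and 23 per arm, it would rise from 0.83% to about 5% to 19%.

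**What to change.** 1. Correct the sentence in the Blinding section to say that the assessor will be blind to the randomization status and will not take part in the intervention. It then agrees with the Abstract and the randomization section.
2. Confirm in writing how assessments have been done since 17 March 2024. If any were made by someone who knew the allocation, flag those visits before database lock, disclose them, and add a sensitivity analysis of the primary outcome without them.
3. As supporting safeguards, state that only the independent allocation staff hold the code list, and keep follow-up 25(OH)D results from assessors and participants until database lock, since those results could reveal the arm.

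The cost is one corrected sentence, through the ethics committee approval that the protocol requires for any change, and an instruction to the site. Identical capsules and independent allocation are already in place, so blinding the assessor needs no new resources. The sensitivity analysis is needed only if unblinded visits are found.

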### Procedure for unbinding if needed

Unless a major unfavorable event happens, such as hypercalcemia or kidney stones, blindness will be kept in place under normal conditions. The trial’s unblinded participants will thereafter be terminated, and their medical issues will be treated appropriately.

### Study interventions

Pirotta and his colleagues found that daily supplementation with 2,000 IU vitamin D3 for 10 weeks in older adults significantly increased knee extension muscle strength by 8–11% but did not reach the statistically significant group difference compared with the placebo group [23]. In another previous study, 50 older adults with vitamin D levels < 20 ng/ml took 4000IU daily vitamin D supplement, and 78% of aged older adults had 25(OH)D levels ≥ 30 ng/mL after 6 months [24]. The doses of 4000 IU vitamin D3 daily have also been reported to be required to achieve plasma 25(OH)D levels associated with lowest disease risk in observational studies in older adults [25]. Vitamin D group will receive 4000 IU/day for six months, modified from the earlier research [23–25]. Subjects will be randomized into 2 study groups: (1) Intervention group: patients receive daily dose of 4000 IU of vitamin D3 supplements. (2) Control group: patients receive placebo. Supplements will be dispensed to participants in baseline and 1^st^ follow-up to increase the subject compliance.

All study capsules, including the placebo, will be manufactured according to Good Manufacturing Practice (GMP) guidelines for quality assurance (see Fig 2). All capsules purchased from SODX Co., Ltd, Osaka, Japan, and patients in the control arm will receive an identical inert placebo provided by the same company. As a placebo will look and taste like vitamin D3, this can ensure the participants are blinded to the treatment. Utilizing a placebo that closely mimics the appearance and flavor of vitamin D3 will effectively blind the participants to their treatment.

**Fig 2 pone.0309610.g002:**
[figure not shown]
Vitamin D3 supplement or placebo.

### Adverse events, safety and modifications

The upper tolerable intake level for vitamin D in the general population has been set at 4000/IU daily [26]; as this is a long-term treatment program, the self-reported harm effects remain uncertain. Research staff will monitor and handle participant concerns regarding discomfort. Medical staff will also evaluate whether immediate removal from the study is necessary for their best interest to safeguard their health. Any unfavorable incidents or adverse events that develop throughout the study will be brought to the attic committee.

A significant adverse event must be notified to the Hong Kong Hospital Authority Research Ethics Committee within twenty-four hours of the incident. Until the serious adverse event is resolved or finished, the primary investigator will be in charge of managing it. The trial steering group and investigators will determine whether a minor or significant adverse event is related to the study intervention. The principal investigator will promptly stop the intervention if the reported event is connected to it and advise the patient to seek medical attention.

### Adherence and satisfaction

Patients will be required to keep personal diaries with information on their medications. Additionally, the study team will increase adherence by calling the patients once a week to check on them. The research staff will contact patients who miss a scheduled session and ask them to reschedule at a different time within a week. When a patient refuses to participate in the study, the researchers will only withdraw them from it after making several unsuccessful attempts to get in touch with and persuade them. Participants can also stop participating in the study at any time for any reason; if they do, they will be asked if they want to be contacted again according to the trial schedule. Participants will be encouraged to report the incidence of falls in the study period.

Satisfaction and feedback will be recorded based on the following questions at 0-month, 3-month, 6-month and 12-month follow-up assessments.

Are you satisfied with the vitamin D supplementation? (1 = Very Dissatisfied, 2 = Dissatisfied, 3 = Neutral, 4 = Satisfied, 5 = Very Satisfied)How effective do you feel the vitamin D supplementation has managed your knee osteoarthritis symptoms? (1 = Not effective at all, 2 = Slightly effective, 3 = Moderately effective, 4 = Highly effective, 5 = Extremely effective)Do you have any additional comments or feedback regarding your experience with the vitamin D supplementation?

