## Introduction

One of the most prevalent chronic degenerative disorders is osteoarthritis (OA) of the knee. Older adults who experience it become disabled, causing discomfort and stiffness. Among persons over 60, the prevalence of radiologic knee OA was 37.4%, while that of symptomatic knee OA was 12.1% [1]. With just 4300 total knee replacements conducted in 2021, the Hospital Authority (HA) had over 26,000 patients on its waiting list for knee total knee replacements (TKRs), meaning that the estimated waiting period in Hong Kong was about 89 months [2]. The number of people with end-stage knee OA who are waiting for surgery is anticipated to rise sharply as the population ages. While waiting for TKR, patients with end-stage OA can benefit from additional therapies to help them function better and maintain overall health.

Patients with end-stage knee OA frequently give up on physical activity to prevent joint stiffness and pain, which can negatively impact overall muscle health and localized knee function. As people age and become less active, their muscular mass and strength gradually decrease to an unusually low level known as "sarcopenia" [3]. Older adults with sarcopenia are more likely to have a decline in functional outcomes and a greater death rate, which puts a strain on their finances and healthcare system [4]. On the other hand, sarcopenia was found in 32.8% of patients with end-stage knee OA in a previous study on the prevalence of sarcopenia in end-stage knee OA patients. These patients likewise recovered more slowly following TKR [5]. A recent study categorized “sarcopenic knee OA” patients as a new subgroup with a higher risk of falling and associated risk factors than patients with sarcopenia or knee OA alone [6]. Strengthening exercise has been indicated to improve muscle mass, strength, and gait speed among sarcopenic patients [7]. However, the individual responses to exercise are variable [8].

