**Fig 1 pone.0309610.g001:**
[figure not shown]
SPIRIT schedule of enrolment, intervention, and assessments. This figure includes participants’ recruitment, allocation, intervention, and outcome assessments.

Initial ethics approval and consent to participate have been obtained from the Joint Chinese University of Hong Kong–New Territories East Cluster Clinical Research Ethics Committee (CREC no. 2022.252), in accordance with the declaration of Helsinki (See S2–S4 Files with initial ethic approval, the updated ethics approval, Chinese and English versions of consent forms, and approved protocol). The trial was registered on clinicaltrials.gov (NCT05981534).

All participants will be required to provide written informed consent prior to enrollment. The informed consent process will be conducted by a trained research staff member, who will explain the study purpose, procedures, potential risks and benefits, and the participants’ right to withdraw from the study at any time without penalty. Participants will be given sufficient time to review the informed consent form and ask any questions they may have before signing.

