#### Potential ethical concerns

*Risks of vitamin D supplementation*. While vitamin D supplementation is generally considered safe, there is a small risk of hypercalcemia or other adverse effects. Participants will be closely monitored. Any participants who develop significant adverse events will be withdrawn from the study and provided with appropriate medical care.

*The burden on participants*. The study involves multiple visits and assessments over 12 months, which may be burdensome for some participants. To mitigate this, participants will have flexible scheduling to accommodate their needs.

*Confidentiality and data protection*. All participant data will be de-identified and stored securely. Only the research team will have access to the identifiable data, and any publications or presentations will ensure participant anonymity.

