### Outcomes and outcome assessments

The primary outcomes will be muscle strength using quadriceps and hamstring muscle assessments, and the secondary outcomes will be the post-intervention change in muscle strength function from baseline using 5-time chair stand test, sarcopenia assessment by Dual Energy X-ray Absorptiometry (DXA), handgrip strength and 6-meter gait speed test, six questionnaires: Western Ontario and McMaster Universities Osteoarthritis Index (WOMAC), Knee Injury and Osteoarthritis Outcome Score (KOOS), Short-Form 36 (SF-36), International Physical Activity Questionnaire (IPAQ), Nutritional Intake and Sunlight Exposure questionnaire (Questionnaires can be seen in S5 File), and biochemical assays including serum Vitamin D level and myokines. Blood samples will be taken under non-fasting conditions. The serum obtained will be immediately stored at -80°C until analysis.

Outcome assessments of the patients will be performed at baseline (0 month), 3 months and 6months after the commencement of vitamin D supplement, and 6-month after the interventional period.

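### The only stated method for recording falls is passive, although a fixed question in the existing calls and visits would cost little; the 24-hour reporting rule also needs its start point and recipient reconciled

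*Protocol article*

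**What the plan says.** **Falls.** The section on adherence and satisfaction contains the one instruction on recording them: "Participants will be encouraged to report the incidence of falls in the study period". The same section describes two tools that could carry such information and gives each another purpose. On telephone contact, "the study team will increase adherence by calling the patients once a week to check on them". On diaries, "Patients will be required to keep personal diaries with information on their medications". It also prints the satisfaction and feedback questions asked at 0, 3, 6 and 12 months; none concerns falls or injury.

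**Visits.** The section on outcomes and outcome assessments states: "Outcome assessments of the patients will be performed at baseline (0 month), 3 months and 6months after the commencement of vitamin D supplement". The sentence goes on to a further assessment six months after the intervention period, that is, month 12. Falls are not among the outcomes listed there.

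**Why falls are relevant.** The Introduction cites a study that described patients with sarcopenic knee osteoarthritis as "a new subgroup with a higher risk of falling".

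**General safety.** Under potential ethical concerns the article says: "Participants will be closely monitored". The adverse-events section has research staff deal with participants' concerns about discomfort.

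**Reporting rule.** The adverse-events section says that a significant adverse event "must be notified to the Hong Kong Hospital Authority Research Ethics Committee within twenty-four hours of the incident". The sentence before it sends all adverse events to a committee whose name is garbled, apparently a slip for the ethics committee. The section on ethics approval records approval by the joint university and "New Territories East Cluster Clinical Research Ethics Committee (CREC no. 2022.252").

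**The concern.** A count obtained by encouraging people to report depends on who remembers and chooses to mention a fall as well as on who falls. The protocol itself cites falls as a risk in a subgroup relevant to this population, and it already pays for frequent contact with every participant. Leaving the question out of that contact gives away information that would be nearly free. At stake is the completeness of a safety count.

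The reporting rule raises a smaller, separate matter. A deadline that starts at the incident can expire before anyone on the team knows of the event, so staff may be in breach through no fault of their own. Staff working to a 24-hour limit also need to know which committee to notify, and the article uses more than one name.

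**Working it through.** The plan states no figure on this point, so there is none to reproduce. The check compares the relevant sections and adds one simple illustration.

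**1. Falls: method stated against contact available**

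| Contact | Stated purpose or content | Falls question stated? |
|---|---|---|
| Weekly call | Adherence, checking on patients | No |
| Diary | Medication information | No |
| Visits at 0, 3, 6, 12 months | Outcome assessments; satisfaction and feedback items | No |
| General instruction | Participants encouraged to report falls | Self-report only |

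Over six months of treatment (about 183 days), weekly calls amount to 183 / 7 ≈ 26 per participant, or 26 × 56 ≈ 1,456 in all. Three visits after baseline come on top of that. The opportunity to ask therefore already exists.

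**2. The 24-hour clock**

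Assumption, not made in the documents: an event happens at a random time between two contacts and is first learned of at the next one. The share known within 24 hours is then 1 day / contact interval in days.

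- Learned of the same day from the patient, family or hospital: 100%.
- Learned of at a weekly call: 1/7 = 14%, so 6/7 = 86% would be late; mean delay 7/2 = 3.5 days.
- Learned of only at a visit three months after the previous one: 1/91 ≈ 1%.

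The rule can be met for events reported promptly and is usually missed for events disclosed late. The range of about 1% to 100% shows that compliance depends on how the team hears of the event, which a clock starting at the incident ignores.

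**3. The recipient**

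| Section | Body named |
|---|---|
| Ethics approval | Joint university and New Territories East Cluster committee |
| Adverse events, significant events | A Hospital Authority research ethics committee |
| Adverse events, all events | Garbled name, apparently the ethics committee |
| Data management; protocol amendments | The ethics or ethical committee, unnamed |

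The names differ. The text does not say whether they denote one body or two.

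**The case against.** The strongest reply is that falls are not an objective, an outcome or an analysis variable, so the trial loses nothing it planned to estimate. The article condenses an approved protocol held in supplementary files, and call scripts and event forms usually sit there. Participants receive an identical placebo, so incomplete self-report should be similar in the two arms: counts are lost, but no route to differential bias is evident. Weekly calls, visits and general monitoring all give participants occasions to mention a fall.

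Most of this stands, and it limits the point. A missing falls form is no finding in itself. What remains is that the article does state a method, the method is passive, and a better one fits into contacts already being made.

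A reader might infer several stronger conclusions that the documents do not support:

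- *That falls reach the record only if volunteered, or that harms in general are under-counted.* No falls question is stated for calls or visits, but the article does not exclude one, and the argument concerns falls alone.
- *That there is no contact from month 6 to month 12.* The article gives no end date for the calls. That they stop with the capsules is an inference, and so is any figure built on it, such as 1/183 ≈ 0.5% of events known within 24 hours.
- *That a definite number of fallers is missed.* Assuming that 20% to 40% of 56 participants fall in a year (11 to 22) and that self-report catches 50% to 80%, the number missed is 11 × 0.2 ≈ 2 up to 22 × 0.5 = 11. Both rates are guesses, so the result is no estimate for this trial.
- *That the 24-hour rule cannot be met.* It can, whenever the event is reported promptly.
- *That reports would go to the wrong committee.* The Hospital Authority name may be a loose label for the approving body.

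**Conclusion.** The point holds as a low-cost improvement to safety recording. The stated method for falls is passive although frequent contact already exists, so fall counts are likely to be incomplete, by an amount the documents do not allow to be sized. No planned outcome, comparison or analysis is affected. The judgement assumes that the full protocol does not already script a falls question; if it does, the article needs only a sentence saying so.

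The reporting rule is a secondary matter of wording. A deadline counted from the incident cannot be guaranteed for events learned of later. The 14% figure applies only to events first learned of at a weekly call and does not predict overall compliance. The committee names are inconsistent and must be reconciled; two separate bodies are not shown.

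**What to change.** **Main change.** Add one fixed, identically worded question on falls, injury and new symptoms to every existing weekly call and scheduled visit, in both arms, and record the answer each time, including when it is no. Report the counts by arm descriptively as safety data, without a formal test. The cost is slightly more call time and more minor events logged; no new contact is needed. The trial-status section reports recruitment as still ongoing, so the change would help data not yet collected.

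**Secondary changes in the adverse-events section.** Run the 24-hour limit from when the research team becomes aware of the event. Reconcile the committee names with the ethics-approval section so that one recipient is identifiable, or state that two bodies receive the report, and correct the garbled name. The cost is a few words.

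**Optional.** State whether the calls continue after month 6. If they do not, a brief monthly call until the month-12 visit would mean about five per participant (5 × 56 = 280 in all). This is an added procedure, not the correction of an error, and the main change does not depend on it.
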